### Support worker engagement

A support worker will regularly attend the participating schools to increase pupil awareness of what is available in the area, provide advice on how to access activities and encourage pupils to design new activities or attract new coaches to the area. The support worker will audit the activities available and monitor voucher usage monthly to identify those engaging well and those not engaging with the project. Each month, the support worker will host drop-in style sessions in school lunchtimes so that pupils can liaise regarding their ideas and current engagement with the vouchers, and raise any questions or clarify any issues they may have. Feedback from these sessions will be used to target new activity providers that pupils have specifically expressed interest in.

Regular contact with the schools will aid communication, and maintain a presence to help pupils and teachers feel supported by the project. Assemblies will be held at the schools, to directly update the year group with important information regarding their vouchers and activity providers, also providing a general summary. The support worker will also communicate with local activity providers to create new activity options and ensure vouchers remain redeemable throughout the 12-month intervention.

### Control schools

Control schools are encouraged to continue with their usual practice throughout the duration of the study. They will receive a mindfulness course for staff or pupils because of their participation in the study at baseline, 6 months, 12 months and 18 months.

## Data collection

Data collection periods will take place at three time points: baseline, 6 months, 12 months and 18 months follow-up for both intervention and control schools (Fig. 1). Quantitative measures of fitness, PA, motivation and cardiovascular health will be assessed at all four time points using the measures described below, in addition to focus groups and interviews to assess qualitative aspects of the project.

**Fig. 1 Fig1:**
[figure not shown]
Data collection and Intervention time scale

### Cardiovascular fitness (Cooper run test)

The CRT is a 12-min walk/run test that will be performed at all four time points to assess cardiovascular fitness. The validity of the CRT as a predictor of aerobic fitness has been tested by numerous studies in both young males and females [35–37]. The test will be performed as part of normal PE lessons in the schools to avoid disruption to school timetables.

### Physical activity (Actigraph accelerometers)

Physical activity will be measured via Actigraph GT3X+ accelerometers (Actigraph, Pensacola, Florida, United States), a tri-axial accelerometer which has previously been used in adolescents both for hip and wrist placement [38, 39]. The accelerometers will be worn on the non-dominant wrist of the participant, as opposed to the hip, for improved compliance [40]; a methodology adopted by the recent National Health and Nutrition Examination Survey (NHANES) between 2011 and 2012. The Actigraphs will be worn for seven full days at all times, apart from bathing or swimming, and will be set to record at a frequency of 30 Hz.

### Motivation (exercise motivation questionnaire (BREQ-2))

The modified Behavioural Regulation in Exercise Questionnaire (BREQ-2) is a 19- item questionnaire that provides scores for amotivation and external, introjected, identified and intrinsic regulation. It is an accessible questionnaire, clearly written to aid pupils understanding of the questions. The BREQ-2 has been noted to obtain good psychometric information [41] and has been previously used to provide information regarding teenager’s motivation to exercise [42–44]. The questionnaire will be administered at all four time points.

### Cardiovascular health (blood pressure and pulse wave analysis)

Blood pressure will be measured through a standardised upper arm cuff methodology using a sphygmomanometer (Omron M2 monitor, OMRON Healthcare UK Ltd., United Kingdom). Participants will be seated for a minimum of five minutes to allow them to be sufficiently rested prior to any measures being taken. The Omron cuff will be positioned on the upper left arm, with the midline of the cuff positioned over the brachial artery, and the arm out straightened, resting gently on a table so as not to influence the blood pressure reading [45]. The cuff size will be chosen in accordance with recommendations to ensure adequate fit for all participants [45]. The cuff will be inflated until a blood pressure recording appears on the Omron M2 monitor screen, at which point the cuff will deflate. This process will be repeated twice more, allowing the average of the three measures to be taken. Should any of the measures be very different (+/− 5 mmHg) an additional measure will be taken.

To further assess vascular function, non-invasive measurement of pulse wave analysis will be undertaken as an indicator of arterial stiffness [46]. Pulse wave analysis will be assessed using the Vicorder (Skidmore Medical Limited, Bristol, United Kingdom). Participants will be seated and a SC10 Hokanson cuff positioned around their upper left arm. Once the participant has rested for five minutes, the cuff will be gradually inflated according to an inbuilt automated protocol, during which the brachial artery pulse-pressure waveform is recorded. Central augmentation pressure and augmentation index are determined from the waveform using a transfer function integral to the software. This process will be performed a second time, if both measures of augmentation pressure are within ±5 mmHg of each other and augmentation index are within ±5% the two measures are accepted, if not a third reading is taken and a mean of all 3 taken.

### Adolescents’ views (focus groups)

Semi-structured focus groups will consist of 6–8 pupils with boys and girls in separate groups (two focus groups per school). Participants will be asked their opinions regarding what physical activity is, its barriers and what could be done to improve activity in their areas. Intervention schools will discuss the ACTIVE project specifically (See Topic Guides: Appendix one). Baseline focus groups will consist of pupils of randomly selected consented pupils. After this, participants purposively selected from consented pupils to gain a variety of viewpoints from those engaging well with the intervention and those who are not. The focus groups will provide ACTIVE with a greater understanding of the mediating factors that influence teenage physical activity. These will also help provide context to the quantitative measures from baseline to 18 months.

In addition to focus groups with teenagers, focus groups and interviews will be held with stakeholders (e.g. Active Young People Officers from the local council and teachers from intervention schools) to inform the process evaluation of ACTIVE. These will be held at the 6 month, 12 month and 18 months data collection time points.

## Analysis

CONSORT guidelines will inform the analysis and presentation of the study [47]. Multilevel regression analyses will test the effect of the intervention on our primary and secondary outcome measures in comparison with the control arm. We will adjust for baseline, 6 month, 12 month and 18 month follow-up scores and baseline characteristics (e.g. sex). Focus groups will be analysed via thematic analysis in order to identify key themes from discussions with pupils involved in the project [48]. Quantitative measures will be linked to the SAIL databank to analyse the impact of physical activity levels on educational attainment and GP visits. COREQ (Consolidated Criteria for Reporting Qualitative Research) will be followed for the qualitative aspects of the research.

This RCT will examine change in the intervention group compared to controls. Findings from the feasibility study showed that sedentary behaviour reduced by 65 min (95% CI: 12.0 to 117.6) from baseline (*n* = 75). A previous study [49] had an intracluster correlation of fitness scores across 10 schools of 0.16. Therefore, estimating a reduction in sedentary behaviour of 65 min (intervention) and 15 min (control) with a standard deviation of 30 min, and an average cluster size of 150 children per school ICC of 0.16, coefficient of variation of cluster sizes of 0.9, power of 80% and significance of 5% would require 450 children per arm in 3 schools in each arm (6–8 schools in total depending on consent rates).

Fitness improved in the feasibility study in the intervention group by 98 m (95% CI: 19 to 177, children ran 1730 m in 12 min at baseline and 1823.3 m at post intervention). Therefore, estimating improvement in cooper run of 98 m (intervention) and 22 m (control) with average cluster size of 150 children per school and ICC of 0.16 (as above) would require 300 children or 2 schools per cluster (3 schools if consent rate is assumed to be 60%).

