### Primary aims

To examine evidence of the effect of a multi-component intervention in improving cardiovascular fitness based on Cooper Run Test score.

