### Secondary aims

2.To examine evidence of the effect of a multi-component intervention in reducing time spent sedentary, as measured by 7-day accelerometry.3.To determine the effectiveness of the ACTIVE intervention to improve the following secondary outcomes:
The amount of teenagers meeting the recommendation of 60 min of MVPA per day.Cardiovascular health (blood pressure and pulse wave analysis (PWA) an indicator of arterial stiffness).Exercise motivation (BREQ-2).The characteristics of teenagers who engage with the scheme, particularly among high risk groups to determine what works for whom, why and in what contexts.
4.To examine evidence of the effect on sustained local investment in implementing recommendations of teenagers in promoting PA and cost-effectiveness.5.To provide evidence of whether ACTIVE can have a sustainable effect on fitness and PA (18-month follow-up)6.To provide evidence that ACTIVE can be implemented by the local council with future rollout to other areas.7.To undertake data linkage of quantitative measures through the Secure Anonymised Information Linkage (SAIL) databank [28] to analyse the effects of physical activity levels on educational attainment and GP visits.

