## Design

ACTIVE is a mixed methods randomised controlled trial based in state secondary schools in Swansea, South Wales. Schools will be approached to take part due to their: i) location in one of Wales’ most deprived areas and ii) location in a Communities First catchment area [29, 30]. Randomisation will occur prior to baseline data collection with schools randomised into either the intervention arm or control arm. Due to the nature of the study, participants will be aware of which arm they have been allocated to.

The College of Human and Health Science Ethics Committee at the College of Medicine, Swansea University granted ACTIVE ethical approval on 12/05/2016.

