### Physical activity vouchers

The intervention involves provision of vouchers equating to a monetary value of £20 (four vouchers in increments of £5) per pupil each month for 12 months. They are to be distributed in schools with the purpose of being used to; i) spend on existing activities, ii) fund new activities in the schools or communities such as fitness classes, and iii) purchase sporting equipment for themselves or a club. The vouchers are to be treated similar to a cash transaction but without the delivery of change, in order to prevent the purchase of non-PA based items. At the end of each month, vouchers will be collected from each provider with an accompanying invoice for reimbursement of fees. This transaction process has been informed by the ACTIVE feasibility study [7]. Activity providers (for example, leisure centres and sports clubs) have been recruited during the development stages of the project and will continue to be recruited throughout the intervention based on pupil suggestions.

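### The Analysis section lists the 6, 12 and 18 month outcome scores as adjustment covariates; taken at its word, the model cannot be fitted sensibly or does not estimate the total intervention effect

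*Protocol article*

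**What the plan says.** The Analysis section of the protocol article names the model and its purpose: "Multilevel regression analyses will test the effect of the intervention on our primary and secondary outcome measures in comparison with the control arm". The next sentence gives the covariates: "We will adjust for baseline, 6 month, 12 month and 18 month follow-up scores and baseline characteristics (e.g. sex"). The follow-up scores and the baseline variables stand in one list, with nothing to separate their roles.

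Other sections show what the follow-up scores are:

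- Data collection: "Quantitative measures of fitness, PA, motivation and cardiovascular health will be assessed at all four time points", that is, at baseline, 6, 12 and 18 months.
- Physical activity vouchers: these are given "per pupil each month for 12 months". The 6 and 12 month visits therefore fall during and at the end of the voucher period, and the 18 month visit falls after it.
- Primary aims: "To examine evidence of the effect of a multi-component intervention in improving cardiovascular fitness based on Cooper Run Test score".
- Secondary aims: "To provide evidence of whether ACTIVE can have a sustainable effect on fitness and PA (18-month follow-up"). The 18 month score is thus the subject of an aim of its own.
- Design: "Randomisation will occur prior to baseline data collection with schools randomised into either the intervention arm or control arm".

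Nowhere does the article describe the follow-up scores as repeated responses in a longitudinal model, or limit adjustment to baseline values.

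**The concern.** Adjusting for the baseline score is sound: it raises precision and leaves the target of estimation alone. The scores at 6, 12 and 18 months are different in kind, because they are what the intervention is meant to change. If one visit's score is regressed on arm and on the scores at other follow-up visits, the arm coefficient compares pupils who already had equal scores at those visits. Whatever benefit is shared across visits is credited to the covariates and not to the arm. A 12 month analysis would even be adjusted for a later measurement.

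Two aims are affected. The primary aim asks for the total effect on the Cooper run, and the coefficient would be something smaller if the intervention also works at the other visits. The sustainability aim asks whether a gain is still there at 18 months. Conditional on the 12 month score, the 18 month coefficient asks whether the arms moved further apart than their 12 month scores predict. A gain that was fully kept could then look small.

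**Working it through.** **What the sentence literally specifies.** The outcome is measured at four visits and the list names all four. Whichever follow-up visit is analysed, its own score is among the covariates. A 12 month score adjusted for the 12 month score is explained perfectly, and nothing is left for the arm term. To get a model that can be fitted, the reader has to drop the analysed visit from the list. The calculation below does so, and this leave-one-out version is an interpretation and not the article's text.

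**Inputs.**

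- Planned Cooper run improvements, from the Analysis section: 98 m (intervention) and 22 m (control). The difference is 98 − 22 = 76 m. No figure in the plan is disputed here; 76 m only sets the scale.
- Assumed, because the article does not give them: equal variances across visits, the correlation r between visits, and the effect at each visit.
- Expected effect at baseline: 0.

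**Formula.** For target visit t, the arm coefficient is d_t − Σ b_j d_j. Here d_j is the effect at adjusting visit j, and b = S⁻¹c, where S is the within-arm correlation matrix of the adjusting scores and c holds their correlations with the target score.

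**12 month score adjusted for baseline, 6 and 18 months, equal correlation r.** Each slope is b = r/(1 + 2r).

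- r = 0.5: b = 0.5/2.0 = 0.250
- r = 0.7: b = 0.7/2.4 = 0.292
- r = 0.9: b = 0.9/2.8 = 0.321

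| Assumed effect at 6 / 12 / 18 months | r = 0.5 | r = 0.7 | r = 0.9 |
|---|---|---|---|
| 76 / 76 / 76 m: 76 − 2b × 76 | 38.0 m | 31.7 m | 27.1 m |
| 38 / 76 / 38 m: 76 − 2b × 38 | 57.0 m | 53.8 m | 51.6 m |
| Either course, baseline adjustment only | 76 m | 76 m | 76 m |

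The loss is 50% to 64% in the first row (38/76 and 48.9/76) and 25% to 32% in the second (19/76 and 24.4/76).

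**Sensitivity to the correlation pattern.** Suppose instead that the correlation decays with the gap between visits (first-order autoregressive), with a constant 76 m effect. The coefficient is then 76(1 − r)²/(1 + r²). This gives 34.2 m at r = 0.3, 15.2 m at r = 0.5 and 0.4 m at r = 0.9.

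**18 month score adjusted for baseline, 6 and 12 months, fully sustained 76 m.** Under equal correlation the result is again 38.0, 31.7 and 27.1 m at r = 0.5, 0.7 and 0.9. Under decaying correlation it is 76(1 − r), which is 38.0 m at r = 0.5 and 7.6 m at r = 0.9. A gain kept in full would thus be shown as half or less in these cases.

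**Opposite extreme.** If the effect existed only at the analysed visit, every other d_j would be 0 and nothing would be lost.

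**The case against.** The best defence is that the sentence is loose wording for a repeated-measures analysis. The model is multilevel, all measures are taken at four times, the section goes on to speak of change in one arm against the other, and the 18 month result has its own aim. Because the list cannot be run literally, a sensible analyst might read it as accounting for visit. This stands as a statement of what may have been intended. It does not rescue the text: the follow-up scores share a covariate list with sex, and no other sentence makes them responses.

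It may also be said that an article condenses and that an analysis plan will supply the detail. That answers an omission. Here a covariate set is stated, and a plan that did otherwise would contradict the published protocol.

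The objection to the size is stronger. The correlations, equal variances and visit-specific effects are all assumed, and the regression is single-level although the plan is multilevel and uses an ICC of 0.16. Results range from almost no remaining effect to no loss at all, depending on those assumptions.

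A reader might infer that the trial's primary estimate will be biased towards zero by half or more. The documents do not support that: they do not show that the harmful model is the one intended, and they give no figures from which the loss could be fixed. A reader might also infer that 12 months has to be the primary visit. The article names no primary visit for the Cooper run, and that choice is separate from correcting the covariate list.

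**Conclusion.** The concern holds as a wrongly stated covariate rule. Taken at its word, the sentence either adjusts a score for itself or, with the analysed visit left out, yields an arm coefficient that is not the total effect "in improving cardiovascular fitness based on Cooper Run Test score". With positive correlation between visits, that coefficient is attenuated whenever the intervention also works in the same direction at the other visits. For the sustainability aim it would test further change and not persistence.

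The size is illustrative. With 76 m at every follow-up and equal correlation of 0.5 to 0.9, 38 to 27 m remains; with half that benefit at 6 and 18 months, 57 to 52 m remains. These figures rest on assumed correlations and effect courses, equal variances and the leave-one-out reading. The true loss cannot be known from the article, and it would be nil if a repeated-measures model with baseline adjustment was what the authors meant.

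**What to change.** Reword the sentence so that the 6, 12 and 18 month scores are outcomes in the multilevel model, adjusted only for the baseline score and baseline characteristics such as sex. A repeated-measures model with arm-by-visit terms and random effects for pupil and school is one suitable form. It gives the effect at each follow-up visit directly, including the 18 month contrast that the sustainability aim needs.

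The covariates should be called baseline and not pre-randomisation, because the Design section places randomisation of schools before baseline data collection; a strictly pre-randomisation rule would exclude the baseline scores themselves.

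The cost is one sentence of analysis wording. No extra data, visits or pupils are needed.

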## Background

Being active in adolescence is associated with many health benefits [1–6] and physical activity (PA) levels established during this time are likely to be taken into adulthood [2]. However, reports show that many adolescents are not sufficiently active to achieve these benefits [2, 7]. Government recommendations for PA suggest adolescents should be engaging in at least 60 min of moderate to vigorous physical activity (MVPA) every day [8]. A large proportion of young people do not meet this recommendation in Wales [9], with recent evidence showing that only 11% of girls and 20% of boys are sufficiently active [10]. This is concerning, as there is strong evidence to show the increased risk of non-communicable disease such as CHD, reduced well-being and shortened life expectancy resulting from inactivity and low aerobic fitness levels [11, 12].

Given that 7 million people in the United Kingdom are fighting CV diseases, [13] with physical inactivity a major risk factor, the development of effective interventions to promote activity in adolescence is of urgent public health concern [14]. It is reported that one of the main barriers to PA for teenagers is accessibility (e.g. cost and lack of local facilities) [8, 15], particularly for teenagers from disadvantaged backgrounds [4]. There is also a population trend towards spending more time inside, where technology can increase screen time and sedentary behaviours [3, 6].

The Active Children through Individual Vouchers – Evaluation Project (ACTIVE), funded by the British Heart Foundation (BHF) [16], aims to tackle these barriers and increase PA by giving teenagers vouchers to spend on activities of their choice. The project encourages teenagers to access existing provisions or generate their own in order to tackle accessibility issues and create the opportunity to participate in desired activities [15]. Evidence has shown that empowering teenagers to make their own choices over which activity they engage in, the location where they engage, and the people they participate with, can improve activity levels [17]. ACTIVE will also encourage teenagers to express the importance of choice and empowerment in advocacy meetings with stakeholders. As a result, the project aims to enhance socialisation and peer support, in order to facilitate PA uptake. This has been positively associated with teenage activity levels [18].

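### The linked analysis of attainment and GP visits is described as an effect of physical activity level, which is not randomised, and no comparison by arm is clearly stated for these two outcomes

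*Protocol article*

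**What the plan says.** Two places in the protocol article describe the linked analysis, and they agree. Under Secondary aims, aim 7 undertakes linkage through the SAIL databank "to analyse the effects of physical activity levels on educational attainment and GP visits". The Analysis section repeats this: "Quantitative measures will be linked to the SAIL databank to analyse the impact of physical activity levels on educational attainment and GP visits". In both, the exposure is the pupil's activity level and the wording is causal.

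The Design section has "schools randomised into either the intervention arm or control arm". The Analysis section gives a general rule for outcomes: "Multilevel regression analyses will test the effect of the intervention on our primary and secondary outcome measures in comparison with the control arm". Aim 3 opens with "To determine the effectiveness of the ACTIVE intervention to improve the following secondary outcomes" and then lists the 60-minute activity recommendation, cardiovascular health, exercise motivation and the characteristics of pupils who engage. Attainment and GP visits are not in that list.

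**The concern.** Randomisation protects a comparison between intervention and control schools. It does not protect a comparison between more and less active pupils. Pupils are not assigned an activity level, and any level measured after baseline may itself have been changed by the intervention.

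The article supplies a candidate confounder. Its Background section says that poor access to activities is a barrier "particularly for teenagers from disadvantaged backgrounds". Disadvantage may plausibly also bear on school attainment and on use of the GP. For GP visits there is a second route: ill health can lower activity and raise visits, so an association could run from health to activity.

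Two things are at stake. If the text is followed as worded, an observational association would be reported as an effect of activity. And the question the randomised design can address without this confounding, whether ACTIVE changed attainment or GP use, might not be answered for these outcomes.

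**Working it through.** The document gives no figure for this analysis, so there is nothing to reproduce. The check is mainly a reading of the text.

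**Setting the sections side by side**

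1. *Exposure.* Aim 7 and Analysis both name activity level. Neither names arm.
2. *What is randomised.* Design: schools, to one of two arms.
3. *Claim made.* Aim 7 speaks of effects and Analysis of impact.
4. *Is a comparison by arm stated for these outcomes?* The general multilevel sentence covers primary and secondary outcome measures. Attainment and GP visits are absent from the aim 3 list, and the linkage has its own sentence with a different exposure. On the other hand, aim 7 stands under Secondary aims. Sedentary time (aim 2) is also outside the aim 3 list, yet aim 2 is plainly about the effect of the intervention. The aim 3 list therefore does not settle which outcomes the general sentence covers, and the text is unclear.

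**Illustration of what confounding could do**

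The correlations below are assumptions; none is in the document. Suppose activity has no effect on the outcome and one unadjusted confounder has correlation *a* with activity and *b* with the outcome. Then

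- spurious correlation: r = a × b
- test statistic, approximately: m = atanh(r) × √(n − 3)
- two-sided 5% rejection rate: 1 − Φ(1.96 − m) + Φ(−1.96 − m)

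For n, the Analysis section says the trial "would require 450 children per arm in 3 schools in each arm", so 2 × 450 = 900. The 60% consent rate in the same section's fitness calculation gives 0.6 × 900 = 540 if applied to that total.

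Worked case, n = 900, a = 0.2, b = 0.3: r = 0.06; m = 0.0601 × √897 = 1.80; rejection rate 44%.

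| a | b | r | n = 540 | n = 900 |
|---|---|---|---|---|
| 0.1 | 0.1 | 0.01 | 6% | 6% |
| 0.2 | 0.3 | 0.06 | 29% | 44% |
| 0.3 | 0.4 | 0.12 | 80% | 95% |

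Another choice of n is seven schools of 150 at 60% consent: 7 × 150 × 0.6 = 630. There a = b = 0.2 gives r = 0.04, m = 0.04 × √627 = 1.00 and 17%; a = b = 0.3 gives r = 0.09, m = 2.25 and 62%.

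All these rates treat pupils as independent, so they do not describe a multilevel model. They run from almost nominal to almost certain rejection, depending on the assumed correlations.

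**Precision of a comparison by arm**

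The article gives an intracluster correlation of 0.16 for fitness and none for attainment or GP visits. If 0.16 applied, with 0.6 × 150 = 90 pupils per school and equal school sizes, the design effect would be 1 + 89 × 0.16 = 15.24, and 630 pupils would carry the information of about 630 / 15.24 = 41 independent ones. Unequal school sizes would lower this further.

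**The case against.** The strongest reply is that aim 7 is a separate observational aim. It asks how activity relates to attainment and GP use, and for that question activity level is the right exposure and arm is not. Such an analysis is legitimate when it is labelled as an association. That stands, and is why the analysis should be kept. It does not rescue the causal wording, which appears in both places.

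A second reply is a dilemma. Either attainment and GP visits are not trial outcomes, and no comparison by arm is owed; or they are secondary outcomes, and the general multilevel sentence already supplies one. This has force. A reader might infer that the plan rules out a comparison by arm for these outcomes, but the document does not say so. What stands is that the text leaves the matter unclear.

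A third reply is that a condensed article need not list confounders or the linkage model. That is right, and their absence is no part of this point. A reader might infer that the results would necessarily be confounded. The document does not support that, because a fuller plan may adjust for the relevant variables. Open to confounding is as far as one can go. Adjustment would still leave the analysis observational.

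**Conclusion.** The point holds as one of wording and of an unclear analysis. Aim 7 and the Analysis section attach causal language to an exposure that is not randomised, and no section clearly commits to a comparison by arm for attainment and GP visits. As described, the linked analysis cannot by itself show that activity changes either outcome.

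The size of any bias cannot be derived from the document. It would be tempting to quote a false-positive rate, such as 17% to 62%, as a property of this trial. That would be wrong: the rates rest wholly on assumed correlations, ignore clustering, and fall to about 6% when both correlations are 0.1. They show only that the mechanism can matter.

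The consequence is limited to one secondary aim. The primary Cooper Run Test comparison and the outcomes listed under aim 3 are not touched.

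**What to change.** Reword aim 7 and the matching Analysis sentence along these lines:

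*Linked attainment and GP-visit records will be compared between intervention and control schools as randomised, using the multilevel model applied to the other secondary outcomes. The relation of measured activity level to these outcomes will be examined in an exploratory analysis and reported as an association.*

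This removes effects and impact from the activity-level analysis and settles whether a comparison by arm is planned.

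The cost is two edited sentences and one extra model on records already being linked. The drawback is precision: an estimate from seven schools will be imprecise, and the article's sample-size calculations concern sedentary time and the Cooper run, not these outcomes. It should be reported with its confidence interval, and a wide interval should not be read as evidence of no effect.

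### The sedentary-time sample size uses an SD of 30 min, but the feasibility CI in the same paragraph implies about 165 to 230 min, so the stated 80% power is not supported

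*Protocol article*

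**What the plan says.** All the inputs are in the Analysis section of the protocol article. It first gives the feasibility finding, "sedentary behaviour reduced by 65 min (95% CI: 12.0 to 117.6) from baseline", with n = 75. It then takes the clustering from elsewhere: "A previous study [49] had an intracluster correlation of fitness scores across 10 schools of 0.16". From these it plans by "estimating a reduction in sedentary behaviour of 65 min (intervention) and 15 min (control) with a standard deviation of 30 min", with 150 children per school, a coefficient of variation (CV) of cluster size of 0.9, 80% power and 5% significance, and concludes that this "would require 450 children per arm in 3 schools in each arm (6–8 schools in total depending on consent rates").

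No source is given for the SD of 30 min. The Aims section fixes the allocation at 4 intervention and 3 control schools. Sedentary time is listed under Secondary aims. The primary outcome, the Cooper run, has its own calculation in the next paragraph, which does not restate a power.

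**The concern.** The 65 min effect is carried straight from the feasibility study into the planning assumption, so effect and SD must be on the same scale. On that scale an SD of 30 min cannot be squared with the interval reported. With SD 30, 75 pupils would give 65 ± 1.96 × 30/√75 = 65 ± 6.8 min, roughly 58 to 72. The paragraph reports 12.0 to 117.6.

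The SD enters the required sample size as a square, so an error of several-fold changes the answer completely. If the 80% stands in print, a null result for sedentary time could be read as evidence of no effect from a well-powered comparison.

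**Working it through.** **Inputs** (Analysis, except the allocation, which is in Aims): difference 65 − 15 = 50 min; SD 30 min; 150 children per school; ICC 0.16; CV 0.9; 5% significance, taken as two-sided; 3 schools per arm planned, 4 v 3 in the trial; feasibility CI 12.0 to 117.6 with n = 75.

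**Formulas.** Design effect DE = 1 + ((CV² + 1)m − 1) × ICC. Standard error of the difference = SD × √(DE/n₁ + DE/n₂). Power is from the noncentral t with df = number of schools − 2.

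**1. The plan's own figure.** DE = 1 + (1.81 × 150 − 1) × 0.16 = 44.28. With 450 children per arm, SE = 30 × √(2 × 44.28/450) = 13.3 min and 50/13.3 = 3.76. On 4 df the power is 79.9%, which matches the stated 80%. (The normal approximation does not match: it gives 96.4% power, or a requirement of only 250 per arm.) The arithmetic is therefore sound on its inputs.

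**2. The SD implied by the feasibility CI.**
- Half-width: (117.6 − 12.0)/2 = 52.8 min.
- SE: 52.8/1.96 = 26.9 min (26.5 with t on 74 df).
- SD of within-pupil change: 26.9 × √75 = 233 min (229 with t), so about 230.
- If the CI compared two independent samples of 75: 26.9 × √(75/2) = 165 min.
- If the analysis adjusts for baseline with correlation r, the residual SD is SD of change × √((1 + r)/2). From 230 min this gives 163 at r = 0 and 212 at r = 0.7.

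The plausible range is about 165 to 230 min, which is 5.5 to 7.7 times the planning value.

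**3. Power with only the SD changed** (ICC 0.16, CV 0.9, difference 50 min).
- 3 v 3 schools, 4 df: 8.3% (SD 165) and 6.7% (SD 230).
- 4 v 3 schools, 5 df: SE = 165 × √(44.28/600 + 44.28/450) = 68.5 min, power 9.2%; with SD 230, SE = 95.4 min, power 7.2%.

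**4. Sensitivity to the ICC and the CV penalty** (4 v 3 schools, t on 5 df). ICCs other than 0.16 are assumptions.

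| ICC | CV | Power, SD 165 | Power, SD 230 |
|---|---|---|---|
| 0.16 | 0.9 | 9% | 7% |
| 0.16 | 0 | 13% | 9% |
| 0.05 | 0.9 | 18% | 12% |
| 0.02 | 0.9 | 34% | 20% |
| 0.02 | 0 | 50% | 30% |
| 0.01 | 0.9 | 53% | 31% |
| 0.01 | 0 | 69% | 43% |

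**5. Detectable difference at 80% power** (3.51 × SE on 5 df). At ICC 0.16 and CV 0.9 it is 3.51 × 68.5 to 3.51 × 95.4, about 240 to 335 min. At ICC 0.02 and CV 0.9 it is about 90 to 130 min. The plan assumes 50 min.

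**The case against.** The strongest points on the other side concern reach and precision; none removes the contradiction.

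- **The 7-9% is conditional.** It keeps an ICC that the plan borrows from fitness scores, and a CV penalty that a multilevel model, which weights unequal schools, may not fully incur. This stands. A reader might infer that the true power is 7-9%; the documents give no ICC for sedentary time and do not support so exact a statement. A range is needed.
- **The SD of 230 assumes an unadjusted within-pupil change in 75 pupils.** The article does not say how the interval was formed. This stands too, and is why 165 is carried alongside.
- **Sedentary time is secondary.** The Cooper-run paragraph reaches 2 schools per arm, or 3 at 60% consent, by a separate route. So the number of schools does not rest on this calculation alone, and the finding does not show that the primary comparison is underpowered.
- **A standard error may have been entered as an SD.** It is tempting to state this because 27 is close to 30. The two are not equal and the text gives no source for the 30, so it is a possible explanation only.
- **Consent.** A reader might add that 60% consent leaves 270 pupils in 3 control schools instead of 450. The 60% belongs to the Cooper-run calculation, and the sedentary sentence already allows for consent through its 6 to 8 schools. It also barely matters: with the plan's inputs and 3 v 3 schools, 90 instead of 150 per school moves power from 79.9% to 79.5%.

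**Conclusion.** The concern holds in this form: the SD of 30 min is contradicted by the feasibility interval in the same paragraph, and the 80% power for sedentary time depends on it. On the feasibility data the SD is about 165 to 230 min. With the plan's own ICC and CV, power for 50 min with 4 v 3 schools is then about 7-9%. With an assumed ICC of 0.02 it is about 20-34% with the CV penalty and 30-50% without it. Power comes near 80% only when clustering almost vanishes, which is not what the plan assumes.

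The conclusion rests on n = 75 being the number behind the interval, on a two-sided 5% test, and on 150 children per school. It concerns a secondary outcome. It matters because this is the only calculation that states a power, and it is the source of the 450 children per arm.

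**What to change.** - Replace the SD of 30 min with the value computed from the feasibility dataset: the SD of change, or the baseline-adjusted residual SD if that matches the planned model. State which it is and how the interval was obtained.
- Withdraw the 80% power claim for sedentary time.
- State the power for 50 min and the detectable difference for the 4 v 3 schools over a range of ICCs, saying that 0.16 is a fitness ICC, and with and without the cluster-size penalty.
- Say that sedentary time is secondary, and that a null result on it will be read through its confidence interval.

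The cost is one re-run of the calculation and some rewording. Neither the design nor data collection changes; the stated power for this outcome falls.
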